## Abstract

**Background:**

Arthroscopic rotator cuff repair is described as being a successful procedure. These results are often derived from clinical general shoulder examinations, which are then classified as 'excellent', 'good', 'fair' or 'poor'. However, the cut-off points for these classifications vary and sometimes modified scores are used.

Arthroscopic rotator cuff repair is performed to improve quality of life. Therefore, disease specific health-related quality of life patient-administered questionnaires are needed. The WORC is a quality of life questionnaire designed for patients with disorders of the rotator cuff. The score is validated for rotator cuff disease, but not for rotator cuff repair specifically.

The aim of this study is to investigate reliability, validity and responsiveness of WORC in patients undergoing arthroscopic rotator cuff repair.

**Methods/Design:**

An approved translation of the WORC into Dutch is used. In this prospective study three groups of patients are used: 1. Arthroscopic rotator cuff repair; 2. Disorders of the rotator cuff without rupture; 3. Shoulder instability.

The WORC, SF-36 and the Constant Score are obtained twice before therapy is started to measure reliability and validity. Responsiveness is tested by obtaining the same tests after therapy.

## Background

Arthroscopic rotator cuff repair is performed with increasing frequency. In more than 90% of the patients results are reported to be good to excellent[1-9]. However, the question remains what good to excellent really means. Especially, the University of California Los Angeles (UCLA) Shoulder Rating Scale and Constant Score are used frequently [1-9].

Authors use these instruments to classify results as 'excellent', 'good', 'fair' or 'poor'. Unfortunately the cut-off points vary and some authors use modified scores, making it difficult to compare results [1,4,5,8,10-12] as illustrated in Table 1.

**Table 1 T1:** Publications considering rotator cuff repair using various versions of UCLA Shoulder Rating Scale and Constant Score and different cut-off points to translate the score into a qualification.

Article	Study population	Score	Translation to quality	Result
Tauro 1998[4]	53 arthroscopic RC repair	Modified UCLA	Good: 36-40 Excellent: 41-45	92% good/excellent

Gartsman 1998[10]	73 arthroscopic RC repair	UCLA Constant Patient satisfaction as item of the UCLA ASES SF-36	UCLA: Poor: 0-20 Fair: 21-27 Good: 28-33 Excellent: 34-35	UCLA: 84% good/excellent Satisfaction: 90% good/excellent

Burkhart 2001[8]	59 arthroscopic RC repair	Modified UCLA	Poor: < 29 Good: 29-33 Excellent: 34-35	95% good/excellent

Wolf 2004[5]	95 arthroscopic RC repair	Modified UCLA	Poor: 0-20 Fair: 21-27 Good: 28-33 Excellent: 34-35	94% good/excellent

Iannotti 1996[11]	46 open RC repair	Adjusted Constant Score pain and function questionnaire	Poor: < 70 Fair: 70-79 Good: 80-89 Excellent: 90-100	88% good/excellent

Lam 2004[12]	69 open repair massive RC tears	Constant Score Oxford Shoulder Questionnaire	Poor: < = 50 Fair: 51-65 Good: 66-80 Excellent: > = 81	Constant: 44% good/excellent

Boileau 2005[1]	65 arthroscopic RC repair	Adjusted Constant Score UCLA MRI	No translation described	Constant: 92% good/excellent

The UCLA Shoulder Rating Scale is a combination of physical examination and subjective evaluation of complaints of patients by the attending physician. No publications are available with respect to the development and validation of this instrument. Therefore it is unknown why the developers of this instrument assigned the various weights to the 5 domains. While not necessarily incorrect, it is thus far unsupported[13]. The Constant Score also consists of a combination of physical examination and subjective evaluation filled out by the attending physician. The publication by Constant et al[14]. does not describe the methodology according to which the instrument was developed and more specifically, the rationale for item selection and relative weighing of the items[13].

Both scores are filled out by the attending physician. Kirkley et al. stated that it had been shown that physicians tend to evaluate their patients functioning better than the patients perceive it themselves, making it important for measurement tools to be self-administered[15].

Validated outcome measures need to be used in randomized controlled trials of interventions for rotator cuff tears. In such trials, disease specific quality of life questionnaires could be a core outcome domain [16] in addition to pain, shoulder specific function, and work ability. Most therapies in orthopaedic medicine are designed to improve quality of life rather than to prolong a patient's life. Therefore, it is important to assess quality of life when such therapies are evaluated. Arthroscopic rotator cuff repair is also performed to improve quality of life, which depends on shoulder functioning relevant for day-to-day activities. Hence, health-related quality of life patient-administered questionnaires (HRQL-questionnaires) are needed[15]. The Western Ontario Rotator Cuff Index (WORC) is a disease-specific quality of life questionnaire (QoL-questionnaire) designed for patients with disorders of the rotator cuff (DRC), which was published in 2003 [15] with a clear description on how the items were chosen, formulated and weighted. For further details of WORC we refer to the appendix section.

The WORC is used in research [17] and has already been translated into German [18], Iranian [19], Norwegian [20], Portuguese [21] and Turkish [22]. A Dutch translation of the WORC will be used in our clinic. This translation was performed by linguistic validation, which is not a literal translation but a stepwise process to produce a conceptually equivalent of the original questionnaire[23]. The process was controlled with final approval by one of the authors of WORC[15]. In this study the Dutch version of the WORC is validated.

As far as we know the WORC has not been tested on a group of patients with arthroscopic rotator cuff repair. In the WORC article by Kirkley et al[15]. validity as an evaluative tool was tested in a group of 50 patients with disorders of the rotator cuff (DRC) who reported that their symptoms had changed. Forty-six were treated with injection therapy and only four underwent subacromial decompression[15]. In order to use the test in those who underwent arthroscopic rotator cuff repair, the WORC should be tested in a group of patients treated with this type of repair.

The aim of this study is to investigate reliability, validity and responsiveness of WORC in patients undergoing arthroscopic rotator cuff repair. Because there is no gold standard we are aiming to assess construct validity, i.e. the extent to which WORC scores relate to SF-36 and Constant Scores. More experiences with the disease specificity of the use of the WORC are needed, since this instrument is designed for use in patients with DRC only.

Therefore, three groups of patients are chosen in which the WORC will be tested. These groups contain patients with respectively:

1. Arthroscopic rotator cuff repair;

2. DRC without rupture;

3. Shoulder instability.

We hypothesize that the Dutch translation of WORC:

• has a high reliability (ICC > 0,9) in all 3 groups;

• has a high validity compared to SF-36 and Constant Scores in groups 1 and 2. We expect correlations on the SF-36 and Constant Score to lie around 0.6 and an inverse correlation between Constant Score and SF-36 versus WORC around -0.5[22]; The relation is expected to be negative due to the construction of WORC, in which a high score corresponds to a disabled shoulder, while a high Constant Score and SF-36 match with little disability.

• has a high responsiveness in groups 1 and 2;

• will be more specific to determine the extent of complaints and change in time supposed to be caused by therapy in patients in the groups 1 and 2 when compared to patients in group 3.

It is the experience of orthopaedic surgeons, also mentioned in textbooks[24,25] that patients with a rotator cuff tear (group 1) suffer pain and weakness when they use the ruptured part of the rotator cuff. In patients with DRC (group 2) patients show tendonitis resembling, more continuous, pain. For instance in this group, inability to raise the arm is rather caused by pain than by lack of strength. Patients with instability (group 3) in general complain about dislocations, subluxations or a sense of instability[26,27]. For this group of patients it is easier to avoid provocative movements compared to patients with rotator cuff disease.

The WORC consists of 5 domains: (1) physical symptoms, (2) sports and recreation, (3) work, (4) social function, and (5) emotions. We expect that the scores for each domain will not differ significantly from each other in group 1 and 2, because Kirkley stated that the frequency importance products of the 21 items have a narrow range[15]. On the contrary, based on our experience as orthopaedic surgeons, we assume that especially the domains physical symptoms (1) and social function (4) in group 3 will be rated better, because in the first domain many items involve pain and in the 4^th ^domain the provocative actions would be avoided easier by patients with instability. Resulting from these expectations, we assume that the responsiveness in group 3 will be low for domain 1 and 4.

Unique in our study design is that the patient selection and assignment into subgroups is performed in a continuing clinical process, including both interventions at the outpatients' department and surgical interventions. In this dynamic clinical setting patients can be transferred between the subgroups and inclusion can be performed continuously.

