## Methods/Design

### Patient assignment

The WORC, as a disease-specific evaluation instrument, was developed for patients with a DRC[15]. In order to investigate reliability, validity and responsiveness of the WORC in patients with arthroscopic rotator cuff repair, data from patients undergoing an arthroscopic rotator cuff repair are analysed (group 1). To investigate disease-specificity of the WORC when compared to a different DRC, a second group 'non-Ruptured DRC' is added (group 2). This group includes the rest of rotator cuff pathology like rotator cuff tendonitis and tendinosis[15]. Bursitis and calcifying tendonitis are also included in non-Ruptured DRC. A third group consisting of patients with 'Shoulder Instability' is included in order to investigate the disease-specificity of WORC when compared to a different shoulder disease (group 3). Each group will consist of 30 patients in which we assume that at least one group will differ 25% on WORC score from the other groups, which yields an 80% power with a one sided α of 5%. This would also provide ample power for test-retest reliability with correlation coefficient of at least 0.95[28].

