## Appendix

### Description of WORC and item selection

The Western Ontario Rotator Cuff Index (WORC) [15] is designed for patients with disorders of the rotator cuff[15]. It is an HRQL-questionnaire that has 21 items representing 5 domains, each with a visual analogue scale-type response option. The 5 domains are (1) physical symptoms, (2) sports and recreation, (3) work, (4) social function, and (5) emotions. WORC items are scored on a 100-point scale (ranging from 0-100). The most symptomatic score is 2100, and the best, or asymptomatic, score is 0. To present this in a more clinically meaningful format, the score can be reported as a percentage of normal by subtracting the total from 2100, dividing by 2100, and multiplying by 100. Total final WORC scores can, therefore, vary from 0%, the lowest functional status level, to 100%, the highest functional status level [59].

Items for the WORC were derived from published health status scales, functional measures of the shoulder, discussions with healthcare professionals, and interviews with 30 patients from a registry of 150 with rotator cuff pathology. Both professionals and patients were asked to identify ways in which the shoulder condition affected quality of life in general and the 5 domains in particular. The 30 patients interviewed included males and females, aged 30-76, with different degrees of rotator cuff pathology from tendinitis to massive tears.

An original list of 321 items was reduced to 76 by the investigators eliminating duplicated, incomprehensible or ambiguous items. A random selection of 100 patients from the same registry were then asked to indicate whether they experienced each of the items, and to rate the importance of the symptom/disability to their overall shoulder functioning. A frequency importance product was calculated for each item and the 50 items with the highest values were correlated with each other. For every pair of items with coefficients greater than 0.6, one of the items was eliminated, resulting in the final 21 questions. It is not clear whether this criterion applied to items across domains because the only example provided included 3 items from the same domain[60].

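### The expected flat WORC domain profile in groups 1 and 2 is framed as non-significance, which cannot show equality at 30 per group; the group 3 contrast needs one stated comparison

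*Protocol article*

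**What the plan says.** The domain predictions stand in the narrative of the Background, after the bulleted hypotheses. For the two rotator cuff groups the authors expect that "the scores for each domain will not differ significantly from each other in group 1 and 2". The reason given is that a property of the 21 items used in building the questionnaire varies little between items. For the instability group they assume that "especially the domains physical symptoms (1) and social function (4) in group 3 will be rated better", and from this that "we assume that the responsiveness in group 3 will be low for domain 1 and 4".

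The Methods do not mention domains. The sample size text under Patient assignment says "Each group will consist of 30 patients", on the assumption that "at least one group will differ 25% on WORC score from the other groups", and adds a remark on test-retest reliability. The Responsiveness section plans a comparison of WORC scores between the three groups. The Appendix says of the instrument: "It is an HRQL-questionnaire that has 21 items representing 5 domains". It gives a conversion to percent of normal for the total score.

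**The concern.** Two inferences are at risk.

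- **Equality from non-significance.** The only yardstick attached to a flat profile in groups 1 and 2 is that differences are not significant. No margin or interval is given. Under such a yardstick, low power counts in favour of the prediction.
- **A profile difference from two separate findings.** The text opposes one profile (flat, groups 1 and 2) to another (domains 1 and 4 better, group 3). A non-significant result in one set of patients and a better score in another do not show that the two differ. That requires a direct comparison of the domain pattern between groups. It is also unclear whether "especially the domains physical symptoms (1) and social function (4) in group 3 will be rated better" means better than the other domains within group 3, or better than the same domains in groups 1 and 2.

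At stake is what may be concluded about the domain pattern, which is one part of the article's argument that the WORC behaves differently in instability than in cuff disease.

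**Working it through.** **Inputs.** From the article: 30 patients per group, three groups, five domains. Not in the article, so assumed: the SD of the difference between two domains (SD_d = 20 points on a 0 to 100 scale, range 15 to 25), equal correlations between domains, two-sided 5% tests, and one domain shifted from the other four.

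**1. The plan's own figure.** The 30 per group is for a between-group difference, not for domains. No SD is stated. Reading 25% as 25 points, n = 2(1.645 + 0.842)² SD² / 25² = 30 gives SD = 25 × √(30 / 12.37) = 38.9. So the figure cannot be checked, and it says nothing about power for within-patient domain differences.

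**2. One pair of domains, paired t, n = 30.** The noncentrality is (δ / SD_d) × √30. For δ = 5 this is 0.25 × 5.48 = 1.37, and the result is non-significant 74% of the time. For δ = 8 it is 0.40 × 5.48 = 2.19, giving 44%.

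**3. Omnibus repeated-measures F over five domains, n = 30.** The error variance is SD_d² / 2 = 200. The noncentrality is 30 × δ² × (4/5) / 200, with 4 and 116 degrees of freedom and critical F = 2.45.

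| Shift of one domain | Noncentrality | Non-significant, one group | Range for SD_d 15–25 |
|---|---|---|---|
| 5 points | 3.00 | 76% | 59.5–84% |
| 8 points | 7.68 | 43.5% | 16–62.5% |

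If the same shift exists in both groups, both tests are non-significant about 0.765² = 58% and 0.435² = 19% of the time.

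**4. All ten pairs, unadjusted paired t, simulated, SD_d = 20, n = 30.**

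| True shift | All ten non-significant, one group | In both groups |
|---|---|---|
| 0 | 71% | 50% |
| 5 points | 40% | 16% |
| 8 points | 14% | 2% |

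The miss rate therefore depends heavily on a test that the article does not name. Under this reading the expectation would also fail about half the time when all domains are truly equal.

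**5. Equivalence as an alternative.** The margin is ±10 points (assumed), SD_d = 20, true differences zero, and the 90% interval must lie inside the margin. For one pair, power is 70% at n = 30 and 97% at n = 60. A flat profile needs all ten pairs, and then power is about 15% at n = 30 and 82% at n = 60 (groups 1 and 2 together).

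**6. The group 3 contrast.** For each patient, take the mean of domains 1 and 4 minus the mean of domains 2, 3 and 5. With equal correlations its SD is SD_d × √[(1/2 + 1/3) / 2] = 0.645 × SD_d, which is 9.7 for SD_d = 15 and 12.9 for SD_d = 20. For 30 against 60 patients the standard error is that SD × √(1/30 + 1/60) = 0.224 × SD, or 2.17 and 2.89. The difference detectable with 80% power is (1.96 + 0.84) × SE, or 6.1 and 8.1 points.

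**The case against.** The best reply is that this is an expectation in the Background. It is outside the bulleted hypotheses and has no test, alpha or decision rule attached, and the analysis sections never mention domains. A reader might infer that the authors will declare the domains equal after a non-significant test; the article does not say so. A reader might also take the lack of a named group-by-domain test as an error. It is not one, because a journal article may leave that to an analysis plan that is not shown. Both parts of this reply stand and limit the point.

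The size can also be disputed. The 74% and 44% miss rates are for a single pair. If all ten pairs were tested without adjustment in both groups, a flat profile would be hard to confirm (16% and 2% under the two shifts). This stands too: no single figure can be called the miss rate of the plan.

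A further tempting reading is that 21 items cannot split evenly over five domains, so raw domain totals would differ by length alone. That is correct arithmetic, but the article nowhere proposes to compare raw totals, and it describes a percentage format for the total. It supports only a scoring clarification.

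Finally, the Discussion itself concedes that the study cannot truly assess disease specificity, so limited weight rests on the domain profile.

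What the reply does not remove is the wording: non-significance is the only criterion attached to a flat profile, and under an omnibus test small to moderate shifts would often pass it.

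**Conclusion.** The point holds as a minor one. As worded, the expectation for groups 1 and 2 cannot support equality of domains, and setting it beside a better rating in group 3 does not test a difference in profile. With an assumed SD of 20 points for domain differences and 30 patients, one shifted domain goes undetected in a single group about 76% (5 points) or 43.5% (8 points) of the time under an omnibus test, and about 40% or 14% under all ten unadjusted pairs. Larger shifts are mostly found: for one pair, a standardised difference of 0.6 is missed about 11% of the time.

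All SDs, correlations and margins are assumptions, because the article gives none at domain level. The documents do not support the stronger conclusions that the study will claim equality from a failed test, or that its domain analysis is invalid.

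**What to change.** - State that each domain is expressed as a percentage of its maximum, and in which direction, since the article describes both a raw score where high is worse and a percentage where high is better.
- In groups 1 and 2, report domain means and between-domain differences with confidence intervals, and do not read non-significance as equality. Claim equivalence only against a margin stated in advance. The power in step 5 shows that 30 patients are too few for this over all ten pairs at ±10 points, and that even pooling groups 1 and 2 is adequate only if the SD is near 20.
- State the comparator for the better rating in group 3, and test the prediction as one pre-stated within-patient contrast at T0: the mean of domains 1 and 4 minus the mean of domains 2, 3 and 5, group 3 against groups 1 and 2 together. Being within-patient, it removes overall severity differences. At T0 no therapy has been given, so treatment modality does not enter.

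The cost is wording only, with no new data or patients. The downside is that the contrast, and any margin, must be fixed before the data are seen, and that pooling groups 1 and 2 sets aside possible differences between them.

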## Methods/Design

### Patient assignment

The WORC, as a disease-specific evaluation instrument, was developed for patients with a DRC[15]. In order to investigate reliability, validity and responsiveness of the WORC in patients with arthroscopic rotator cuff repair, data from patients undergoing an arthroscopic rotator cuff repair are analysed (group 1). To investigate disease-specificity of the WORC when compared to a different DRC, a second group 'non-Ruptured DRC' is added (group 2). This group includes the rest of rotator cuff pathology like rotator cuff tendonitis and tendinosis[15]. Bursitis and calcifying tendonitis are also included in non-Ruptured DRC. A third group consisting of patients with 'Shoulder Instability' is included in order to investigate the disease-specificity of WORC when compared to a different shoulder disease (group 3). Each group will consist of 30 patients in which we assume that at least one group will differ 25% on WORC score from the other groups, which yields an 80% power with a one sided α of 5%. This would also provide ample power for test-retest reliability with correlation coefficient of at least 0.95[28].

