### Responsiveness

Responsiveness, or the ability of an instrument to detect clinically important change, will be determined by calculating the standardized response means and effect sizes on T0 and T2 scores on WORC, SF-36 and Constant scores for the subgroups. The magnitude of the standardized response mean (mean change in score from T0 to follow-up (T2)/standard deviation of change in score) and the effect sizes (mean change in score from T0 to follow-up (T2)/standard deviation of T0 score) will be interpreted using the Cohen standard of greater than 0.20 for small effects, greater than 0.50 for moderate effects, and greater than 0.80 for large effects.

Finally, a comparison of WORC scores between the three distinct groups is made, to see whether WORC scores can differentiate between them. WORC scores will be compared with SF-36 to investigate whether the noted differences correlate with notable clinical differences and can be expressed as MCID's (minimal clinical important differences)[33].

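### The 80% power claim attaches a one-sided 5% alpha to an undirected three-group hypothesis, and cannot be checked because the SD and the meaning of 25% are not given

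*Protocol article*

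**What the plan says.** The sample-size statement is in the protocol article, Methods/Design, Patient assignment. It fixes the size ("Each group will consist of 30 patients") and then gives the effect, the power and the sidedness in one clause: "at least one group will differ 25% on WORC score from the other groups, which yields an 80% power with a one sided". The alpha level there is 5%. No SD, reference mean, test, contrast or time point is given. The text does not say whether 25% is absolute or relative.

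The matching analysis is described at the end of the Responsiveness section: "a comparison of WORC scores between the three distinct groups is made, to see whether WORC scores can differentiate between them". It is equally undirected and names no test.

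A direction appears in the Background, where the authors expect that "especially the domains physical symptoms (1) and social function (4) in group 3 will be rated better". This singles out two of the five domains of one group. It is not a statement about the total WORC score, and the sample-size sentence does not refer to it.

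The Appendix says that the WORC total of 0 to 2100 can be reported as a percentage of normal from 0% to 100%.

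**The concern.** A hypothesis that at least one of three groups differs from the others is an omnibus alternative. The usual test is a three-group F test, which has no sides. A one-sided alpha belongs to a single comparison with a direction fixed in advance. The sentence combines the two, so its 80% seems to belong to a simpler and more powerful test than the hypothesis calls for.

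This is the only quantified power figure for the 90 patients, and it supports the known-groups part of the validation described in the Discussion. If it came from a one-sided two-group formula, the power of the three-group comparison is lower than stated. If it came from something else, the reader cannot tell what.

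**Working it through.** **Inputs from the protocol article:** n = 30 per group, three groups (N = 90), difference 25%, power 80%, alpha 5% one-sided (Patient assignment); score range 0-100% (Appendix). **Assumptions, because the article gives no value:** SDs of 20 and 25 points, and a mean of 50 for the relative reading.

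**1. Reproducing 80% with the test that fits a one-sided alpha.** For a two-group t test with 30 per group, df = 58 and the one-sided 5% critical value is 1.672. The non-centrality is d·√(30/2) = 3.873·d, where d is the difference divided by the SD. Power is 80% at d = 0.650 (non-centrality 2.517). The normal approximation is close: √(2/30) × (1.645 + 0.842) = 0.642. So 80% is attainable, but for a directed two-group comparison.

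**2. The same d in tests that fit an undirected hypothesis.**
- Three-group F test at 5%, one group shifted by d. The non-centrality is 30 × (2/3) × d² = 20·d² = 20 × 0.650² = 8.45; the critical value F(2, 87) is 3.10. Power is about 73%.
- Two-sided pairwise t test at 5%, critical value 2.002. Power is about 70%.

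These results depend only on d, so the shortfall of about 7 to 10 percentage points holds whatever the SD. For 80% power the F test needs a non-centrality of 9.97, that is d = √(9.97/20) = 0.706.

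**3. What the 25% would have to mean.**

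Read as 25 points on the 0-100% score (equivalently 0.25 × 2100 = 525 on the raw total):
- One-sided pairwise, 80% power: SD = 25/0.650 = 38.5.
- F test, 80% power: SD = 25/0.706 = 35.4.
- For scale, scores spread evenly from 0 to 100 have SD 100/√12 = 28.9. The largest possible SD is 50, so 35 to 38 is wide but not impossible.
- At SD 25, power is 98.5% one-sided pairwise and 98.2% by F test. At SD 20 both are 99.9%.

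Read as 25% of an assumed mean of 50, that is 12.5 points:
- SD 20, d = 0.625: 77% one-sided pairwise, 69% by F test.
- 80% one-sided pairwise needs SD = 12.5/0.650 = 19.2 (19.5 by the normal approximation).

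**4. A single contrast that fits the design.** For group 3 against groups 1 and 2 together (30 versus 60), the standard error in SD units is √(1/30 + 1/60) = 0.224. The normal approximation for a two-sided 5% test with 80% power is (1.960 + 0.842) × 0.224 = 0.63; the t distribution gives d = 0.633. That is 12.7 points at SD 20 and 15.8 points at SD 25.

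**The case against.** The strongest reply is that nothing shows the 80% to be wrong. Under the relative reading, a mean of 50 and an SD a little over 19 return it with a one-sided two-group test, and those values are not strange. This stands: a reader might infer from the 25-point reading that the figure is an arithmetic error, or that no natural reading reproduces it, and the article supports neither.

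A reader might also conclude that a one-sided test has no valid form here. That goes too far. A directional contrast fixed in advance, such as group 3 scoring better than the other two, would be valid, and the Background comes close to supplying one. What remains is that the sample-size sentence does not use it: it speaks of any group differing, and the Background direction singles out two domains.

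Two further inferences should be resisted. One is an inflated family-wise error from several unadjusted one-sided tests; the article names no such analysis. The other is that the 25% contradicts the expectation about domains 1 and 4. The text says these domains especially, not only these, and turning that into a required difference per domain needs weights and zero effects that the article does not state.

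It is also fair that a condensed article may leave the SD and the time point to a fuller document. Alone, those omissions would be missing detail. The mismatch between hypothesis and sidedness is different, because it is in what is printed.

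Finally, the impact is limited. The same paragraph gives test-retest reliability as a separate justification for the group size, and under the 25-point reading with SD 20 to 25 the sample is more than adequate.

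**Conclusion.** The concern holds in a limited form. As written, the 80% is tied to a one-sided 5% alpha that does not match the undirected three-group hypothesis, and no group, contrast or direction is named for the total score. If 80% is right for a one-sided two-group test, it is about 73% for the F test and about 70% for a two-sided pairwise test. That comparison needs no assumption about the SD, only a common SD, normal scores and one shifted group.

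The 80% is unverifiable, not refuted. Depending on the unstated SD and the meaning of 25%, the sentence can describe a study with power above 98% (25 points, SD 20 to 25) or one with 69% by F test (12.5 points, SD 20). Those SDs and the mean of 50 are assumptions made for illustration. The known-groups comparison is not shown to be in danger. The sentence should be corrected, but the point is not critical.

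**What to change.** Restate the power for a test that matches the hypothesis, with 30 per group unchanged. Either of these will do:

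- **Three-group F test at 5%:** 80% power for d = 0.71 when one group is shifted.
- **One prespecified two-sided 5% contrast, group 3 versus groups 1 and 2 together (30 versus 60):** 80% power for d of about 0.63, that is 12.7 points at an assumed SD of 20 or 15.8 points at 25.

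In either case give the difference in absolute points on the 0-100% score, the assumed SD and its source, and the time point of the comparison. Before treatment (T0) is the natural choice for the contrast. Name the same test in the sentence on the group comparison under Responsiveness.

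The cost is one rewritten sentence and no added patients. The small downside of the contrast is that it does not test group 1 against group 2; that comparison would be reported as secondary.
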